1.9. Phase of the trial: Phase III

1.10. Primary goal:

To evaluate the virological response, the specific cytotoxic response to HIV and the point of stabilisation of viremia after the fourth cycle of interruption of anti-retroviral treatment (ART), and the proportion of patients who do not require ART at the end of study following the administration of subcutaneous, low doses of IL-2.

1.11. Experimental design:

A single-centre, non-comparative, prospective, open-label, clinical pilot study.

1.12. Disease being studied:

HIV-1 infection.

1.13. Main evaluation variables:

The proportion of patients presenting plasma viral load (VL) three times greater than the base value (prior to ART), or VL >20 copies/mL where base VL <10 copies/mL;

The proportion of patients with good cytotoxic response after the fourth cycle compared with the beginning of the treatment;

The proportion of patients having been administered with IL-2 not requiring ART at the end of the study. (>350 CD4 cells or VL <55,000 copies/mL).

1.14. Test population:

The study will include eight HIV infected, outpatients having begun highly active antiretroviral treatment (HAART) during primary infection.

1. Duration of the treatment:

The treatment will be administered daily from the first interruption of ART with a subcutaneous dose of 125,000 mIU/m2 for six weeks. After completing four cycles of six weeks, the treatment with IL-2 will be stopped. Patient follow-up will be conducted for two years.

1.16. Schedule and anticipated date of conclusion:

The aim is to start the trial, provided authorisation has been obtained, in November 2001. The recruitment period will last two months, and the follow-up will last two years. The aim is to finish the study in December 2003.

***

**2. Contents** page

1. Summary 2

2. Contents 5

3. General information 6

4. Rationale and objectives 8

5. Trial type and design 12

6. Subject selection 13

7. Description of the treatment 15

8. Trial development and response evaluation 17

9. Adverse events 19

10. Ethical aspects 21

11. Practical considerations 22

12. Statistical analysis 23

13. References 25

Annexes:

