- Another patient treated with DDI, hydroxyurea and indinavir stopped the treatment and presented a rebound in viremia. The patient went back into treatment, after which VL decreased; treatment was then stopped again. Viremia did not rebound and remained at the same level for more than one year without treatment. The patient presented good cytotoxic response to HIV [12].

- Three patients with stable viremia were treated with a combination containing hydroxyurea under the following schedule: three weeks of treatment, one week of interruption followed by two cycles of three months therapy with interruption and resumption of treatment once VL went back up (>5,000 copies/mL). VL became undetectable (<400 copies/mL) after each return to treatment. The relapse-free intervals increased by seven days after the first interruption and went up to 37 days after the third interruption [12].

-*Rhesus macaques* infected with SIV/Mac251 (basal viremia: 200,000 copies/mL, 500,000 copies/mL and 1.1 million copies/mL) were treated with hydroxyurea, DDI and a derivative of adefovir following an intermittent schedule (two cycles of three weeks of treatment followed by interruption). SIV was allowed to rebound to >5,000 copies/mL. Although VL rebounded, in three cases it was controlled and stabilised to a low level of viremia in the absence of treatment. This level was >5,000 copies/mL and was maintained for six weeks during the first interruption and reduced to <200 copies/mL at the lowest and maintained for ten weeks during the third interruption. Two of the monkeys continued without relapse after four and six months respectively [12].

The intermittent interruption of treatment is associated with a strengthening of the cytotoxic response to HIV that can contribute to a prolonged suppression of VL when treatment is withdrawn.

1. *Acute suspension of treatment is acceptably safe*

Chronic exposure to sub-therapeutic levels of anti-retrovirals can promote resistant mutations and lead to a loss in efficacy. Nevertheless the abrupt interruption of treatment does not seem to be associated with the formation of resistance. In the cases of interruption of the treatment, viral proliferation originates in viral reservoirs in non-activated T lymphocytes. Numerous studies have demonstrated that the virus remaining in the reservoirs is sensitive to ART [13].

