**7. Description of the treatment**

Patients will stop antiretroviral treatment for eight weeks and will return to it for eight to twelve additional weeks with the addition of interleukin-2 for six weeks.

This process will be repeated four times. Upon finishing the four cycles, treatment with IL-2 and ART will be suspended unless there has been evidence of viral replication to the point that viral load (VL) reaches a stable level. (Definition of point stabilization: equal VL in three sequential determinations separated by at least three weeks)

a) Doses, intervals, method and form of administration and duration

Interleukin-2 (IL-2), 125,000 units/m2/day, subcutaneously, for six weeks

b) Criteria for modifying the protocol during the trial:

 INTOLERANCE/TOXICITY

Interleukin-2: the tolerance of the medication will be evaluated at each visit with a view to its suspension in cases where the severity or intensity of adverse effects so prescribe.

 SAFETY MEASURES

Because of concerns over an eventual appearance of resistance and a loss of antiretroviral treatment efficacy, various measures have been designed to ensure that intermittent therapy will be immediately discontinued in case there is a failure to:

- Analyse the response to treatment in the weeks leading up to each interruption. VL will be measured at seven weeks after restarting treatment in each cycle. The study will be stopped if more than two favourable responding patients reach VL <50 copies/mL.

- The study will only be interrupted between weeks 64 to 80 in those patients who show lowered VL after the third interruption compared with the first interruption.

- ART will be started in patients with CD4+ lymphocyte count <350 cells/µL or with an HIV-1 plasma VL >55,000 copies/mL in two consecutive determinations (27). In asymptomatic patients with CD4+ lymphocyte count between 350-500 cells/µL and/or VL between the previous levels, the evaluation of resuming ART will be done on an individual basis.

- There will be a safety commission.

c) Concomitant medications:

Any concomitant medication will be reflected appropriately in the DCN (detailing the product, dose, administration method, day of administration, reason for the treatment, etc.).

1. Salvage medication:

ART will be started in patients with CD4+ lymphocyte count <350 cells/µL or with an HIV-1 plasma VL >55,000 copies/mL in two consecutive determinations (27).

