**8. Trial development and response evaluation**

a) Main evaluation variables (activity and effectiveness):

- To determine the proportion of patients with VL increases at least three times greater than the baseline (prior to ART) (corresponding approximately to an increase of 0.5 log).
- To determine the proportion of patients with specific cytotoxic response to HIV
- Compare the level of viremia stabilisation at stopping ART by comparing viremia at the end of the fourth cycle and at the end of the study with pre-HAART viremia.
- Determine the proportion of patients not requiring ART at the end of the study.

b) Secondary variables (safety and tolerance):

- Description of adverse events

c) Number and timing of visits and tests or examinations.

Medical visits will be carried out during the first week of the study, then every fortnight for four months and then every two months until the end of the study. During the periods of treatment interruption analyses will be carried out weekly. During the periods of treatment the analyses will be monthly.

An amygdala biopsy will be taken at the beginning and at the end of the study

See calendar (p. 18).

d) Duration of the study:

Two and a half years from the date of the first patient inclusion. The recruitment period should be two months and the duration of the study 24 months from the date of the last patient inclusion.

Calendar of the visits and tests or examinations.

| Determination | 0 | 8 | 16[[1]](#footnote-2) | 24 | 32 | 40 | 48 | 56 | 64 | 72 | 80 | 88 | 96 | 104 | 112 | 120 | 128 | 136 | >136 |
| --- | --- | --- | --- | --- | --- | --- | --- | --- | --- | --- | --- | --- | --- | --- | --- | --- | --- | --- | --- |
| VL (limit of detectability = 10) | a | a | a | a | a | a | a | a | a | a | a | a | a | a | a | a | a | a | Every 4 weeks |
| Complete blood count | a |  |  |  |  |  |  |  | a |  |  |  |  |  | a |  |  | a | Every 8 weeks |
| CD4 | a |  |  |  |  |  |  |  | a |  |  |  |  |  | a |  |  | a | Every 8 weeks |
| Histocompatibility[[2]](#footnote-3) | a |  |  |  |  |  |  |  |  |  |  |  |  |  |  |  |  |  |  |
| Cytotoxic function in response to HIV and CD4 helper function[[3]](#footnote-4) | a |  | a |  | a |  | a |  | a |  |  |  |  |  | a |  |  |  | Every 16 weeks |
| Integrated HIV DNA  In peripheral mononuclear cells (PMC) | a |  | a |  | a |  | a |  | a |  |  |  |  |  | a |  |  |  | Every 16 weeks |

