**12. Statistical analysis**

a) Statistical tests:

- Descriptive analysis:

The descriptive analysis will include variables referring to demographic data and clinical events related to the sample as well as adverse reactions in terms of absolute and relative frequency, means and standard deviations, medians and ranges.

*Indications for antiretroviral treatment*

Spanish recommendations for ART (27) prescribe that it should not be given to patients who are asymptomatic with CD4+ lymphocyte cell count <500 µg/L and a viral load <10,000 copies/mL. The proportion of patients presenting both criteria will be determined at two points: 1) when VL reaches the set-point following the last withdrawal from treatment; and 2) at the end of the study (week 120-136).

- Comparative Analysis

*1) Increase in plasma VL in the* ***eighth*** *week following withdrawal, and 2) proportion of patients with cytotoxic response to HIV.*

- Comparison will be made between cycles one, two, three and four.

An increase in VL is defined as being at least three times greater than the baseline (prior to ART) (corresponding approximately to an increase of 0.5 log).

- In patients with a VL <10 copies/mL (undetectable), an increase will be considered as being any value >20 copies/mL after two weeks since the interruption of treatment.

- A more sensitive analysis will compare the second, third and fourth cycles with the first cycle, for each patient, as paired data. McNemar’s test will be used to compare discordant results: i.e., N pairs with a higher value for the first cycle and a lower value for the fourth cycle, with the N pairs from the opposite situation. The same considerations will be applied to the evaluation of the cytotoxic capacity and function of CD4 *helper* lymphocytes, which will be recorded as positive vs. negative or good vs. weak versus according to the stimulation index.

*2) Analysis of VL increase time above 5,000 copies/mL.*

- The treatment will be stopped in weeks 64-80, if viremia in week 56 is less than in week eight.

- The increase time will be compared (measurement history) with that of other groups (see references 2 and 3)

3) *Multivariant analysis*

A ‘response’ is defined as the lack of a rebound or the absence of indications for ART on multiple occasions following the interruption of treatment.

The indicating response factors will be evaluated by means of multiple regression analysis, and will include:

- CD4 count before ART,

- VL before HAART,

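### The fixed 16-week sampling grid for cytotoxic response meets the cycle ends only if every ART phase lasts exactly 8 weeks, so a main variable is read at drifting points of the cycle

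*Protocol*

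**What the plan says.** Section 1.13 of the protocol lists among the main variables "The proportion of patients with good cytotoxic response after the fourth cycle compared with the beginning of the treatment". Section 12, under the comparative analysis, applies the following to cytotoxic response as well as to viral load: "Comparison will be made between cycles one, two, three and four". It adds a paired analysis of cycles 2, 3 and 4 against cycle 1 with McNemar's test, and extends it to cytotoxic capacity and helper function.

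Section 7 defines the cycle: "Patients will stop antiretroviral treatment for eight weeks and will return to it for eight to twelve additional weeks". It continues: "This process will be repeated four times".

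In the Section 8 calendar, the row "Cytotoxic function in response to HIV and CD4 helper function" is marked at weeks 0, 16, 32, 48, 64 and 112. It is blank at weeks 72 to 104 and 120 to 136, and has a 16-weekly entry in the column beyond week 136. Footnote 1, attached to the week-16 column of the same calendar, describes a different cycle: 10 weeks long, with 2 weeks off treatment.

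**The concern.** The sampling weeks are fixed calendar weeks, but the cycles they are meant to represent vary in length. Any ART phase longer than 8 weeks pushes later cycles to the right while the samples stay where they are. The sample labelled with a cycle then sits earlier and earlier in that cycle.

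This matters because the phase of the cycle is not neutral for this variable on the protocol's own account. Section 4 states: "The intermittent interruption of treatment is associated with a strengthening of the cytotoxic response to HIV". A reading after 8 weeks back on ART and a reading during an interruption need not measure the same thing, even if nothing has changed between cycles. The paired comparison would carry that difference along with any real change. With eight patients and a positive/negative or good/weak reading, one patient who changes category moves the proportion by 1/8 = 12.5 percentage points. No later analysis can recover a sample taken at the wrong point, so this cannot be left to a statistical analysis plan.

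**Working it through.** **Inputs.** Off-ART phase 8 weeks, ART phase *a* = 8 to 12 weeks, four cycles (Section 7). Samples at weeks 16, 32, 48, 64 and 112 (Section 8 calendar). Final stop window from Section 12: "The treatment will be stopped in weeks 64-80, if viremia in week 56 is less than in week eight".

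**Step 1: reproduce the plan's own figure.** Four cycles end at 4 × (8 + 8) = week 64 at the earliest and 4 × (8 + 12) = week 80 at the latest. This is exactly the window of weeks 64 to 80, so Section 12 relies on the Section 7 cycle and expects cycles longer than 16 weeks.

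**Step 2: place each sample in its cycle.** Take the same *a* in all four cycles. Cycle *k* starts at week (*k* − 1)(8 + *a*), and ART returns 8 weeks later. For the sample at week 16*k*, the time since ART return is

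r = 16*k* − (*k* − 1)(8 + *a*) − 8 = 8 − (*k* − 1)(*a* − 8).

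If r is above 0, the patient has been back on ART for r weeks. If r is 0 or below, the patient has been off ART for 8 + r weeks.

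| ART phase (weeks) | Week 16 (cycle 1) | Week 32 (cycle 2) | Week 48 (cycle 3) | Week 64 (cycle 4) | Cycle 4 ends | Week 64 is early by | Final stop to week 112 |
|---|---|---|---|---|---|---|---|
| 8 | 8 on | 8 on | 8 on | 8 on | 64 | 0 | 48 |
| 9 | 8 on | 7 on | 6 on | 5 on | 68 | 4 | 44 |
| 10 | 8 on | 6 on | 4 on | 2 on | 72 | 8 | 40 |
| 11 | 8 on | 5 on | 2 on | 7 off | 76 | 12 | 36 |
| 12 | 8 on | 4 on | 8 off | 4 off | 80 | 16 | 32 |

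The last two columns are 4(8 + *a*) − 64 = 4(*a* − 8) and 112 − 4(8 + *a*), in weeks.

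**Step 3: where the on/off state changes.** For cycle 4, r reaches 0 when 3(*a* − 8) = 8, so at *a* = 10.67 weeks. For cycle 3, it does so when 2(*a* − 8) = 8, at *a* = 12. There week 48 falls at the end of the eighth week off ART.

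**Step 4: unequal phases.** If the phases differ, r for cycle *k* is 8 minus the summed excess over 8 weeks of the earlier phases. Weeks 16 and 32 are then always on ART (r = 8, and r from 4 to 8). Week 48 has r from 0 to 8, and week 64 has r from −4 to 8. Cycle 4 ends at week 32 plus the sum of the four ART phases, which equals 64 only if all four last 8 weeks.

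**Step 5: the footnote's cycle.** If every cycle lasts 10 weeks with 2 off, the cycles end at weeks 10, 20, 30 and 40. Week 16 is then 4 weeks on ART in cycle 2, and week 32 is 2 weeks off ART in cycle 4. Weeks 48, 64 and 112 all follow cycle 4. The grid meets no cycle end on that definition.

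**The case against.** The strongest reply is that the grid is right for the shortest cycle, and that for 9- and 10-week phases every sample is still taken on ART. Both statements are true. The on/off mix needs uniform phases above about 10.7 weeks; below that only the time on ART differs, although at 10 weeks it falls from 8 to 2.

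A second reply is that Section 1.10 speaks of the fourth cycle of interruption. The fourth interruption ends at week 3(8 + *a*) + 8, which is no later than week 64 for *a* up to 10.67. On that reading week 64 does follow it over much of the range. The ambiguity is real, but the drift between cycles remains on either reading.

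Third, the calendar has a wider problem. Footnote 1 conflicts with Section 7, and the week-56 viral load shifts in the same way: it is the end of the fourth interruption only if 3(8 + *a*) + 8 = 56, so *a* = 8. Moving one assay row does not settle that, so the cycle definitions must be reconciled too.

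A reader might also infer more than the protocol supports:

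- **That nothing is sampled after cycle 4.** Week 112 follows cycle 4 in every case, and with 8-week phases week 64 is its end.
- **That week 64 precedes the end of the fourth IL-2 course.** This depends on when each course starts. Section 1 has IL-2 running from the first interruption, while Section 7 places it with the return to ART, so no firm statement is possible.
- **That the drift alone would mimic an IL-2 effect.** The protocol gives no on-ART or off-ART levels of cytotoxic response, so the size and direction of any bias are unknown. In a single-arm study that credits interruption itself with an effect, a rise could not be attributed to IL-2 even with aligned samples.
- **That a week-136 sample is wrongly missing.** The main variable is set after cycle 4, and no cytotoxic analysis is fixed at week 136.

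**Conclusion.** The point holds as a mismatch between the sampling calendar and the Section 7 cycle. Over the permitted range, the cycle samples are comparable in phase only if the first three ART phases each last 8 weeks, and week 64 is the end of cycle 4 only if all four do. With uniform phases of 9 to 12 weeks, no sample falls at the end of cycle 4: one is 4 to 16 weeks early and the next is 32 to 44 weeks after the final stop. The comparison between cycles then confounds sampling phase with change in response.

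The tabulated figures assume the Section 7 cycle and equal ART phases within a patient. The protocol does not say how often phases beyond 8 weeks are expected, so the share of patients affected is unknown. The effect on the estimated proportion cannot be calculated from the document.

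**What to change.** First, reconcile the cycle described in Section 7 with the one in calendar footnote 1, so that the cycle ends are defined once.

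Then, in the cytotoxic/helper row of the calendar, replace weeks 16, 32, 48 and 64 with the last on-ART visit of each cycle before the next ART stop. This matches the on-ART state at week 0 and equals the present schedule when ART phases last 8 weeks. In Section 1.13, define the reading after cycle 4 as the cycle-4 sample so placed. Sampling off ART at one fixed point could also make the cycles comparable with each other, but it would not match week 0.

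The cost is a change of calendar wording. The number of samples is unchanged and treatment is not altered. The small downside is that sampling dates will vary between patients. The integrated-DNA and stored-sample rows use the same weeks up to 64, so moving them together would keep a single blood draw.

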**6. Subject selection**

a) Inclusion criteria:

The trial will include patients of both sexes:

1. with diagnosed HIV-1 infection;
2. aged 18 years or older;
3. treated with HAART anti-retroviral treatment (composed of two analogues non-nucleoside reverse transcriptase inhibitors plus a protease inhibitor) since primary infection;
4. plasma viral load <50 copies/mL (Roche Monitor Assay) for at least eight months;
5. CD4 lymphocyte count consistently >500 cells/L (prior to stopping treatment); and
6. who, having been appropriately informed, have granted written consent to take part in the study and to be subjected to tests and examinations that it entails.

b) Exclusion criteria:

1. Patients who have responded suitably to the initial anti-retroviral treatment;
2. patients who have at some time taken nevirapine or efavirenz; and
3. women who are pregnant or lactating, or who intend to become pregnant during the period of the study.

c) Predicted number of subjects:

There will be eight outpatients.

d) Methods for calculating the sample size and data used:

As this is a pilot study, there is no way of knowing what kind of data will be produced in response to this treatment in this subtype of patients with primary HIV infection. The results of this study will allow the calculation of the sample necessary to create a comparison with an appropriate statistical basis.

e) Discontinuation criteria and anticipated analysis of withdrawals and discontinuations:

Patients will be able to leave the study at any time without having to give explanations. Nevertheless, the causes for discontinuation will be collected and recorded in the data collection notebook (DCN).

The researcher will also be able to withdraw patients from the study for reasons of inefficiency, adverse events or patient benefit. The reason for withdrawal will be recorded in the DCN.

All patients who, having been assigned to a treatment group, discontinue the treatment under study or who are withdrawn for any cause will be included in an “intention-to-treat” analysis.

The patients who fail to attend appointments (loss of follow-up) will be considered for the analysis until the moment at which the loss takes place.

f) Dealing with pre-randomisation losses:

Patients who fulfil selection criteria but who, for whatever reason, are not included in one of the treatment groups will be recorded as appropriate (personal, demographic data, etc.), but they will not be included in the analysis.

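### Section 1.13 joins the limits for not needing ART with *or*, so patients who meet the Section 7 ART-start rule count as successes, and Section 12 uses other limits with CD4 pointing the opposite way

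*Protocol*

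**What the plan says.** Four places in the protocol bear on this variable.

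- **Section 1.13 (Main evaluation variables)** counts patients "not requiring ART at the end of the study. (>350 CD4 cells or VL <55,000 copies/mL". Meeting either limit is enough.
- **Section 7 (Safety measures, repeated under Salvage medication)** gives the restart rule: "ART will be started in patients with CD4+ lymphocyte count <350 cells/µL or with an HIV-1 plasma VL >55,000 copies/mL in two consecutive determinations". For asymptomatic patients in an intermediate range, "the evaluation of resuming ART will be done on an individual basis".
- **Section 12(a) (Indications for antiretroviral treatment)** cites national recommendations against giving ART to patients who are "asymptomatic with CD4+ lymphocyte cell count <500 µg/L and a viral load <10,000 copies/mL". It then adds: "The proportion of patients presenting both criteria will be determined at two points". The two points are the viral set-point after the last withdrawal, and study end.
- **Section 8(a)** lists the variable without limits, so it cannot settle which definition applies.

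Two other entries matter. Section 6(a) requires CD4 persistently above 500 before treatment is stopped, and Section 6(c) fixes the sample at eight patients.

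**The concern.** The same two numbers, 350 and 55,000, define both needing ART (Section 7) and not needing it (Section 1.13). The two statements should be opposites, but both use *or*. A patient can therefore meet the start rule and the success criterion at once.

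Section 12 adds a second definition that differs in limits, connector, symptom condition and direction of CD4. Nothing in the protocol says which one produces the reported proportion. An analyst could follow either sentence and get a different answer, and could choose after seeing the data. The ambiguity also reaches the multivariable analysis in Section 12, whose response definition rests partly on the absence of an indication for ART.

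**Working it through.** The protocol gives no planned proportion or power figure for this variable, so there is nothing to reproduce. The check is logical.

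**Inputs.** Start rule from Section 7; success criterion from Section 1.13; Section 12 criterion as printed; n = 8 from Section 6(c). I read every CD4 figure as cells/µL, the unit used in Section 7, and take each viral load below as sustained over two successive measurements.

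**Step 1: the complement.**
Start ART = (CD4 < 350) *or* (VL > 55,000).
Not start = (CD4 ≥ 350) *and* (VL ≤ 55,000).
Section 1.13 = (CD4 > 350) *or* (VL < 55,000).
Apart from values exactly on a limit, the last two lines differ only in the connector. Under Section 1.13, only a patient who fails both limits is counted as requiring ART.

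**Step 2: illustrative profiles.** The values were chosen to fall on each side of every limit; they are not expected frequencies.

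| CD4 | VL | Section 7 starts ART | Section 1.13 (*or*) | Same limits with *and* | Section 12 as printed | Section 12, CD4 sign turned |
|---|---|---|---|---|---|---|
| 600 | 5,000 | no | counted | counted | no | counted |
| 600 | 30,000 | no | counted | counted | no | no |
| 600 | 80,000 | yes | counted | no | no | no |
| 400 | 5,000 | no | counted | counted | counted | no |
| 400 | 30,000 | no | counted | counted | no | no |
| 400 | 80,000 | yes | counted | no | no | no |
| 300 | 5,000 | yes | counted | no | counted | no |
| 300 | 30,000 | yes | counted | no | no | no |
| 300 | 80,000 | yes | no | no | no | no |

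Five profiles meet the start limits. Section 1.13 counts four of those five as not requiring ART; the *and* version counts none. CD4 600 with VL 200,000 twice behaves like the 600/80,000 row.

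**Step 3: Section 12.** As printed, it leaves out 600/5,000, the most favourable row, and would equally leave out CD4 above 500 with undetectable virus. It counts 300/5,000, where Section 7 starts ART. Turning the CD4 sign swaps these two results but does not restore agreement: 600/30,000, 400/5,000 and 400/30,000 are still counted in Section 1.13 and not in Section 12. The limits conflict apart from the sign.

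**Step 4: weight of one patient.** 1/8 = 12.5 percentage points.

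**The case against.** The strongest defence is that this is an eight-patient, non-comparative pilot with no test on this proportion. The variable is one of three main variables in Section 1.13 and one of four in Section 8(a). At 4/8 the exact 95% interval is 15.7% to 84.3%, so no fine inference hangs on it. That limits the consequences, but it does not make a contradictory definition usable.

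Several stronger readings are tempting and are not supported:

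- *Any viral load above 55,000 triggers ART.* Section 7 asks for two successive values and Section 1.13 is silent on this, so a single high value at study end need not trigger a restart. The conflict is clear for patients with two such values or with low CD4. Counts of profiles do not estimate how many patients are affected.
- *A patient already back on ART is scored a success.* The bracket in Section 1.13 looks only at CD4 and viral load, but the phrase it explains arguably excludes someone who has restarted. The text is loose; it does not instruct that scoring.
- *Section 12 scores the best responders as failures.* It sits under a descriptive heading, labels nobody a failure, and does not say that it is the Section 1.13 variable. What stands is that such patients cannot be counted.
- *Lost patients leave the denominator, against intention-to-treat.* Section 6(e) says that they "will be considered for the analysis until the moment at which the loss takes place". It does not remove them from an end-of-study proportion. Its intention-to-treat sentence concerns patients who discontinue or are withdrawn, a different group. How losses enter a proportion may properly be left to a statistical analysis plan.

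A translation or transcription slip may explain the sign and the unit in Section 12. It is still the operative text.

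**Conclusion.** The point holds in this form. Section 1.13 is not the complement of the Section 7 start rule, so a patient who crosses only one limit can meet that rule and be counted as not requiring ART. Section 12 conflicts with both in limits, with Section 1.13 in connector, and in CD4 direction with Sections 1.13, 6 and 7. Its printed unit cannot describe a cell count.

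Each misclassified patient is worth 12.5 percentage points. How many of the eight would be affected cannot be derived from the protocol.

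The conclusion rests on the printed text and on reading all CD4 values on one scale. That the Section 12 direction is out of line is judged from the protocol's own other sections; the cited recommendations were not available. Because following the stated rule would misclassify patients on a declared main variable, it should be corrected before any analysis.

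**What to change.** 1. Reconcile Sections 1.13, 7 and 12 into one definition, used identically in Sections 1.13, 8(a) and 12. Write it as the logical complement of whichever start rule the investigators confirm: limits joined by *and*, with the same two-measurement condition on viral load.
2. State that a patient who is on ART at study end is not counted as not requiring it. This also covers patients restarted by individual decision in the intermediate range of Section 7.
3. Reconcile the CD4 direction and unit in Section 12 with the rest of the protocol and with the recommendations it cites. If the 500/10,000 pair is kept, report it as a separate variable with its own name.

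Which clinical limits apply is for the investigators to decide. The cost is wording in three sections, with no extra patients, visits or measurements called for by this change. The reported proportion can be lower than under the present *or*, because patients who cross one limit would no longer be counted.
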